##### Training and certification plans

All personnel collecting and entering data into the eCRF will have ample training in the trial protocol and eCRF entering. All trial investigators will be GCP certified. Relevant radiological measurements at inclusion and follow-up will be made on clinical scans by trial personnel board certified in neuroradiology. Baseline clinical data will be collected by attending physicians in the neurosurgery department. Neurosurgical or endovascular procedural data will be entered into the eCRF by the operating physician. Follow-up data regarding adverse events will be entered into the eCRF by GCP-certified investigators. Telephone interviews will be done by research nurses trained and certified in structured follow-up assessments on stroke patients.

#### Plans to promote participant retention and complete follow-up {18b}

The study participants are recommended to follow the study protocol. Included participants refusing allocated treatment and crossovers will remain in the study and be included in the intention-to-treat analysis. Additional participants may be enrolled to allow the study to meet its designed sample size dimensions to allow for a sufficiently powered per-protocol-analysis.

Participation in this investigation is voluntary, and the subject may withdraw at any time. All enrolled subjects will be included in data analysis unless they withdraw permission for their data to be used. The sponsor will retain and continue to use any data collected prior to the withdrawal of consent, unless specified by the subject.

In the event the subject chooses to withdraw, he/she will be instructed to contact the Investigator immediately. Withdrawal from the investigation will not affect the subject's standard of care. The subject will be informed of any significant information regarding new findings that may develop during the course of the study that may relate to his or her willingness to continue participation as a study subject.

Subjects will participate in their routine follow-up and allow this data to be gathered. If their participation is terminated, any of their data which has been already gathered will continue to be included. The completion of a subject’s participation in the study or early departure from the study must be fully documented in the subject’s medical records. Subjects will be considered discontinued from the study if any of the following occur:Subject voluntarily withdraws from the study: A subject may withdraw consent from study participation at any time. The subject will be offered to give a reason for their withdrawal. If voluntarily given, this reason will be recorded in the eCRF.Subject withdrawn from the study by the investigator: An investigator may withdraw an enrolled subject from the study for the following reason:

If participation in the study is life threatening for the subject or at the investigators own discretion.

#### Data management {19}

The handling of data, including data quality assurance, will comply with regulatory guidelines (for example GCP and ISO 14155) and the sponsor’s SOPs and work instructions. All steps and actions taken regarding data management and quality assurance will be documented in the sponsor’s SOPs and data handling guidelines. Electronic case report form (eCRF) will be used to collect medical history, subject demographics, procedure-related information, protocol deviations, adverse events, and device deficiencies. The e-CRF will be used for data review, data cleaning, and issuing and resolving queries. This e-CRF is a web-based e-CRF which is password protected and is CFR part 11 compliant. At the end of the study, the data will be stored as a frozen dataset and will be retained.

The e-CRF data from the subjects will be key-coded (pseudo-anonymized). The information related to the subject, e.g., name, is kept separately in the enrollment log at the hospital. Date and time of the procedure and date of discharge will be collected. Exported (image) data will be de-identified. The remaining data will be de-identified. The data will be collected and stored in a secure location.

Completed report forms will be verified against source data and visually checked by the study monitor for completeness, consistency, and legibility.

All adverse event terms recorded on the report forms will be entered into the safety database. All data on the adverse events will be entered into a validated database. Edit checks will be implemented to ensure data quality and accuracy. Responses to requests for further clarification of data recorded in the reports will be answered, dated, and electronically signed by the investigator. Changes will be implemented in the database and the data review and validation procedures will be repeated as needed.

#### Confidentiality {27}

Any physical documentation related to the study are stored in locked premises within the hospital. The PI and local PIs are responsible for this. All data management will comply with regulatory guidelines (for example GCP and ISO 14155), the sponsor’s SOPs and work instructions, and in accordance with the General Data Protection Regulation (GDPR) and national Swedish regulations. The web-based e-CRF is password protected and data from the subjects will be key-coded (pseudo-anonymized). The information related to the subject, e.g., name, is kept separately in the enrollment log in locked premises within the hospital. Exported (image) data will be de-identified. The remaining data collected will be de-identified and stored in a secure location within the hospital.

#### Plans for collection, laboratory evaluation and storage of biological specimens for genetic or molecular analysis in this trial/future use {33}

N/A. No biological material is collected within the trial.

### Statistical methods

#### Statistical methods for primary and secondary outcomes {20a}

All statistical analyses will be performed using SPSS (Armonk, NY: IBM Corp). All performed statistical tests will be two-sided and the statistical significance level set at *p* < 0.05. Baseline characteristics between intervention and control group will be assessed using mean (standard deviation, SD) and median (interquartile range, IQR) for continuous variables and frequency (percent, %) for categorical variables. Differences across groups will be tested using two-sided Student’s *t*-test and Mann–Whitney test for continuous data and the chi-square test for categorical data.

#### Primary variable analyses

The proportional difference in the primary outcome (i.e., proportion of re-operations within 3 months) between intervention and control group will be assessed using logistic regression analysis. Odds ratios (95% confidence interval) will be estimated with adjustment for enrolment center (if applicable) as well as baseline characteristics if these are unevenly distributed across study arms. Kaplan–Meier survival analysis with follow-up time as the time scale will be used to analyze re-operation free survival stratified by enrolment center (if applicable). Difference in survival curves between the intervention and control group will be compared using the likelihood ratio test.

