#### Outcomes {12}

Primary outcome measure:

The primary outcome is the difference in reoperation frequency within 3 months between the two groups. Reoperation is defined as any operative (surgical or endovascular) treatment regarding cSDH on the previously treated side(s).

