#### Secondary variable analyses

Binary secondary outcomes (i.e., technical success rate, all complications rate, and composite outcome of death and re-operation within 3 months) will be analyzed using logistic regression models (as described for the primary outcome). Kaplan–Meier time-to-event analysis with follow-up time as the time scale will also be used to assess the impact of intervention on the composite outcome of death and re-operation with differences between survival curves assessed using the likelihood ratio test. Ordinal secondary outcomes (i.e., mRS and EQ5D) will be assessed at 3 and 12 months after treatment. To assess the effect of intervention at each time point, ordinal logistic regression models will be used. For the continuous secondary outcome (i.e., hematoma volume), a generalized linear model will be used. All analyses will account for enrolment center and baseline characteristics unevenly distributed between study arms when applicable.

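### The primary logistic model adjusts for baseline characteristics only if they turn out uneven between arms, so it is not fixed in advance and gives up most of the benefit of adjustment

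*Protocol article*

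**What the plan says.** Under Primary variable analyses, the proportion reoperated within 3 months "between intervention and control group will be assessed using logistic regression analysis". The odds ratio is to be estimated with "adjustment for enrolment center (if applicable) as well as baseline characteristics if these are unevenly distributed across study arms". Secondary variable analyses extends the rule: "All analyses will account for enrolment center and baseline characteristics unevenly distributed between study arms when applicable".

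The article neither lists the covariates nor says what counts as uneven. The nearest thing to a criterion is the description of the baseline comparison under Statistical methods {20a}: "Differences across groups will be tested using two-sided Student’s *t*-test and Mann–Whitney test for continuous data and the chi-square test for categorical data". The same section sets a general level: "All performed statistical tests will be two-sided and the statistical significance level set at *p* < 0.05". It does not say which of the two tests for continuous variables decides, or that either one triggers adjustment. The section on data transformation also leaves open whether baseline variables are logged or categorised.

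Elsewhere the protocol points to factors it considers important. The Discussion says that bilateral hematomas seem to be reoperated somewhat more often. The section on additional analyses {20b} gives age, comorbidities, drug use and hematoma size as key characteristics, but only for subgroup analyses.

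**The concern.** A covariate belongs in the model of a randomised trial because it predicts the outcome. Observed imbalance is a poor reason, since under proper randomisation every imbalance is chance. The rule stated here has two consequences.

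First, the model behind the trial's single primary test is unknown until baseline data by arm are examined. With no threshold, no covariate list and no coding, two competent analysts could fit different models and both follow the protocol.

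Second, the factors the protocol itself names (bilaterality, hematoma size, age, drug use) stay out of the primary model whenever they balance, which is most of the time. The precision they could give is then lost.

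This is not a detail left to a statistical analysis plan. The protocol states a positive rule, and a later plan that fixed covariates regardless of balance would contradict it.

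**Working it through.** **Inputs from the protocol.** 144 per arm; expected reoperation 17% (control) and 6.5% (intervention); two-sided alpha 0.05; power 80%; likelihood ratio test (all from Sample size {14}); four hospitals (Study setting {9}).

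**Inputs assumed.** The number and strength of prognostic covariates and the criterion for uneven. The documents give none of these, so a range is shown.

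**1. The plan's own figure.** The noncentrality of the likelihood ratio test is 2n[KL(p1, p̄) + KL(p2, p̄)], where KL(p, q) = p ln(p/q) + (1 − p) ln((1 − p)/(1 − q)) and p̄ = (0.17 + 0.065)/2 = 0.1175.
- KL(0.17, 0.1175) = 0.0119 and KL(0.065, 0.1175) = 0.0155.
- 288 × 0.0274 = 7.90, which gives power of 80.3% on 1 degree of freedom.
- 144 per arm is the smallest n that reaches 80%. The stated size is reproduced, and it is an unadjusted calculation.

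**2. How often chance triggers the rule.** For k independent covariates judged at p < 0.05, P(at least one uneven) = 1 − 0.95^k. This is 19% for k = 4, 34% for k = 8 and 46% for k = 12. With 8 candidates there are 2^8 = 256 possible covariate sets.

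**3. Power and type I error by simulation.** 4,000 trials per scenario, 144 per arm, 8 standard normal baseline covariates of which 4 are prognostic, likelihood ratio test for treatment.

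| Assumed log-odds per SD, each of 4 | Power, unadjusted | Power, p < 0.05 rule | Power, 4 covariates always in | Gap, always in minus rule | Type I error, rule | Type I error, smallest p of six readings |
|---|---|---|---|---|---|---|
| 0.3 | 80.6% | 80.2% | 82.5% | 2.3 | 4.8% | 6.3% |
| 0.5 | 81.1% | 80.8% | 84.2% | 3.4 | 4.7% | 6.3% |
| 0.8 | 80.4% | 80.7% | 88.1% | 7.4 | 4.8% | 7.2% |

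The null scenario is 17% in both arms. The six readings are: no adjustment; p < 0.01, 0.05, 0.10 and 0.20; and a standardised difference above 0.1. The Monte Carlo standard error is about √(0.8 × 0.2/4000) = 0.6 points for power and about 0.3 to 0.4 points for type I error.

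**4. Check with three covariates** (assumed log-odds 0.7 per SD, 0.7 and 0.6). Two separate simulations gave:
- rule 82.2%, unadjusted 82.2%, always adjusted 84.8%;
- rule 80.4%, unadjusted 80.6%, always adjusted 83.1% (83.0% with centre terms added).

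The gap between rule and fixed adjustment is 2.6 to 2.7 points. Type I error of the rule was 4.8% and 4.6%.

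**5. Room for covariates.** Expected events are 144 × 0.17 + 144 × 0.065 = 24.5 + 9.4 = 33.8. Treatment plus three centre terms (four centres) uses 4 parameters, or 33.8/4 = 8.5 events per parameter. Three more covariates make 7, or 33.8/7 = 4.8.

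**The case against.** The strongest reply is that the rule does little harm. Selection uses baseline data and not outcomes, and baseline data are entered before allocation is disclosed (Concealment mechanism {16b}). A data management committee independent of the organisers performs the primary outcome analysis ({5d}). The unadjusted analysis already reaches the planned 80%, so the loss is forgone efficiency that rests on assumed covariate strengths. All of this stands and limits the severity. It does not supply the missing model.

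A reader might also infer more than the documents support:

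- **That the rule breaks the 5% error rate.** Applied mechanically it does not. Comparing unadjusted with always-adjusted analyses gives verdicts that differ in 5.5 to 6.1% of trials, and taking the smaller p gives a 6.7% error, but the protocol does not plan an always-adjusted model. Against its own rule the figures are about 1% and 5.2%.
- **That the baseline tests are the declared trigger.** The text never links them to the adjustment. That reading is plausible but is an inference.
- **That centre is chosen from the data.** Dissemination plans {31a} says the first 30 participants inform how many centres are needed, so the qualifier most naturally means: if more than one centre enrols.
- **That the survival comparison competes as the primary test.** The objective, outcome, sample size and opening sentence of the analysis section all concern the 3-month proportion. The statement "Difference in survival curves between the intervention and control group will be compared using the likelihood ratio test" is loosely worded, but a likelihood ratio test from a proportional hazards model is a valid comparison.
- **That the declared quantity goes unestimated.** "The primary outcome is the difference in reoperation frequency within 3 months between the two groups" is general wording and does not commit the trial to a risk difference. An odds ratio is compatible with it.

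**Conclusion.** The concern holds as a matter of prespecification and efficiency. The primary model depends on chance imbalance judged by an undefined criterion, and named prognostic factors are omitted when they balance. Under an assumed p < 0.05 criterion, the rule performs like no adjustment (power about 80 to 82%). It gives up roughly 2 to 7 points against a covariate set fixed in advance, for assumed log-odds of 0.3 to 0.8 per SD on four covariates; weaker covariates would give a smaller loss. Type I error stays at 4.6 to 4.8% and rises to about 6 to 7% only if the most favourable reading of uneven is picked. The sample size is unaffected. This should be fixed because the remedy is cheap and available only before unblinding, but the planned test is not invalid as it stands.

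**What to change.** In Primary variable analyses and Secondary variable analyses, replace the imbalance rule with one model fixed before unblinding:

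- Terms: treatment; centre, if more than one enrols; and about three prognostic baseline covariates with their coding stated. Candidates from the protocol's own text are bilaterality, hematoma size, and age or drug use.
- Include these terms whatever the observed balance, and do not use baseline significance tests to select covariates.
- Keep the unadjusted analysis, and any imbalance-driven analysis, as sensitivity analyses.

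Reporting a risk difference beside the odds ratio and labelling the time-to-event analysis supportive would be useful clarifications, but they are optional.

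The cost is a change of wording. No extra patients or follow-up are needed. The article gives no full list of baseline variables, so the sponsor should confirm that the chosen covariates are recorded; medical history and baseline imaging are already scheduled. The covariates must be committed to in advance, and with about 34 expected events the list has to stay at about three. The simulation with centre terms added showed no material loss of power (83.0% against 83.1%).

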#### Secondary variable analyses

Binary secondary outcomes (i.e., technical success rate, all complications rate, and composite outcome of death and re-operation within 3 months) will be analyzed using logistic regression models (as described for the primary outcome). Kaplan–Meier time-to-event analysis with follow-up time as the time scale will also be used to assess the impact of intervention on the composite outcome of death and re-operation with differences between survival curves assessed using the likelihood ratio test. Ordinal secondary outcomes (i.e., mRS and EQ5D) will be assessed at 3 and 12 months after treatment. To assess the effect of intervention at each time point, ordinal logistic regression models will be used. For the continuous secondary outcome (i.e., hematoma volume), a generalized linear model will be used. All analyses will account for enrolment center and baseline characteristics unevenly distributed between study arms when applicable.

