##### Secondary outcomes

Clinical outcomes: Structured telephone interview with the trial participant will be undertaken at 3 months (2–4 months) and 12 months (10–14 months). Neurological disability will be assessed using the modified Rankin Scale (mRS). mRS is a 6-point grading scale frequently used worldwide in assessing neurologic functionality in stroke and other CNS pathology patients [18]. 0 = no symptoms and 6 = death. Validated questionnaires of mRS are available in Swedish.Quality of Life will be measured using the EuroQoL 5D grading scale (EQ-5D). The EQ-5D is a standardized questionnaire used to measure quality of life in five dimensions—mobility, self-care, usual activities, pain and discomfort, anxiety and depression) and a rating of overall health using a visual analog scale (VAS) [19]. Validated questionnaires in Swedish are available and will be mailed to the participant a week before telephone interview.Change in hematoma volume at 3 months: Routine head NCCT performed at radiology department most conveniently located for the trial participant. Imagery requested and (if applicable) electronically transferred to the research institution through existing secure and firewall protected clinical PACS systems. Relevant measurements processed with automated computer software within the Sectra IDS7 PACS and/or dedicated hematoma measurement software within the Sectra platform (Qure.ai).Technical success: endovascular treatment imagery and associated procedure description or index operational procedure description requested from treating hospital and electronically transferred to research institution. Review of participant eCRF.Safety/adverse events/complications: Subjects’ medical records requested from treating hospital and local hospital and data manually transferred to the eCRF. Neuroendovascular treatment imagery (if applicable) and participant eCRF reviewed.Composite death or reoperation within 3 and 12 months; data from the Swedish National Board of Health and Welfare Statistics Database (reoperation) and National Cause of Death Registry (date of death, primary cause of death) will be collected at 3 months (2–4 months) and 1 year (10–14 months) post procedure.

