#### Data transformation and calculated variables

Data transformation or calculation of variables is not applicable for primary or secondary outcomes. In order to utilize parametric tests, some continuous baseline variables may be subjected to transformation (e.g., log transformation or categorization) in order to assure normal distribution.

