#### Adjustment of significance levels and confidence intervals

The study includes one primary outcome and five secondary outcomes. Threshold for statistical significance is set at *P* < 0.05 for the primary outcome. For secondary outcomes, correction for multiple testing will be performed using a significance level of *p* < 0.01.

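### Haematoma volume is named both as a change and as a residual volume, and baseline volume enters the model only if the arms happen to differ, which gives up precision

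*Protocol article*

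**What the plan says.** Four places in the protocol article describe the same outcome:

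- Secondary objectives (Objectives {7}): changes in volume at 3 months are compared.
- Secondary outcome measures, item III (Outcomes {12}): the residual volume, in mL, on the 3-month CT.
- Secondary outcomes, under data collection {18a}: "Change in hematoma volume at 3 months: Routine head NCCT performed at radiology department".
- Secondary variable analyses {20a}: "For the continuous secondary outcome (i.e., hematoma volume), a generalized linear model will be used", which says neither change nor residual.

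The section Data transformation and calculated variables adds: "Data transformation or calculation of variables is not applicable for primary or secondary outcomes".

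On covariates, Secondary variable analyses says: "All analyses will account for enrolment center and baseline characteristics unevenly distributed between study arms when applicable". Baseline volume is not named. For comparing the arms at baseline, Statistical methods {20a} says "Differences across groups will be tested using two-sided Student’s *t*-test and Mann–Whitney test for continuous data", with significance at 0.05. It does not say that this test decides what counts as uneven.

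On the data available, Training and certification plans says: "Relevant radiological measurements at inclusion and follow-up will be made on clinical scans by trial personnel board certified in neuroradiology". The subgroup section {20b} uses haematoma size as a patient-level factor. On the error level, the section on significance levels says "For secondary outcomes, correction for multiple testing will be performed using a significance level of" 0.01.

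**The concern.** There are two linked problems.

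First, a change and a residual are different variables. Taking change as the absolute difference in mL, the arm difference in change equals the arm difference in residual volume minus whatever chance difference the arms had at baseline. Randomisation makes the two agree on average. In the one trial that is run, the estimate, standard error and p-value will differ. With a fixed 0.01 threshold, the conclusion could depend on which variable is used.

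Second, the case for adjusting for baseline volume rests on how well it predicts 3-month volume, not on whether the arms happen to differ. A rule triggered by imbalance leaves the model unknown until the data are seen, and usually drops a covariate that could narrow the confidence interval. This is not simply detail left to an analysis plan. The article fixes the rule, so an analysis plan that always adjusted would depart from it.

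**Working it through.** **The plan's own figure.** The article gives no sample size, SD or power for haematoma volume. Its 288 belongs to reoperation. The likelihood-ratio formula with 17% against 6.5%, two-sided 0.05 and 80% power gives 143.06 per arm, rounded up to 144, so 288. The figure reproduces, and nothing below changes it.

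**The definitions side by side.** A change score has to be calculated from two scans, and the article says that calculated variables do not apply to secondary outcomes. Residual volume needs no calculation. So the outcome list, the calculated-variables section and a literal reading of the analysis sentence agree on residual volume. The objective and the data-collection label do not.

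**Precision from always adjusting.** Inputs from the article: 144 per arm and two-sided 0.01 for secondary outcomes. Assumed: r, a linear model, and a 3-month scan for every patient. Relative to 3-month volume alone, the variance of the adjusted treatment effect is 1 − r². The sample-size equivalent is 288 / (1 − r²). The effect that the unadjusted analysis detects with 80% power is (2.576 + 0.842) × √(2/144) = 0.403 SD. The last column is the power for that same effect after adjustment.

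| r (assumed) | 1 − r² | 1/(1 − r²) | Equivalent total N | Power at 0.01 |
|---|---|---|---|---|
| 0.2 | 0.96 | 1.04 | 300 | 0.819 |
| 0.3 | 0.91 | 1.10 | 316 | 0.843 |
| 0.4 | 0.84 | 1.19 | 343 | 0.876 |
| 0.5 | 0.75 | 1.33 | 384 | 0.915 |
| 0.6 | 0.64 | 1.56 | 450 | 0.955 |

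**What the imbalance rule keeps.** Suppose that uneven means p < 0.05 on a baseline t-test; the article does not say this. The rule then triggers in about 5% of trials. The part of the variance due to chance baseline difference, r², is removed only in those trials. They carry 2 × (1.96 × 0.0584 + 0.025) = 0.279 of it, so the variance under the rule is 1 − 0.279r². That is 0.989 at r = 0.2 and 0.900 at r = 0.6, against 0.96 and 0.64 when always adjusting. A simulation with 144 per arm and 20,000 runs per value of r agrees: the rule gave 0.99 and 0.92 at r = 0.3 and 0.5, against 0.93 and 0.74 when always adjusting. Under that reading, roughly three quarters of the gain is lost.

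**Against a change score.** Let k be the baseline SD divided by the 3-month SD. The change-score variance relative to 3-month volume alone is 1 + k² − 2rk. For r = 0.3 to 0.6, the ratio of adjusted to change-score variance is 0.24 to 0.25 at k = 2, 0.65 to 0.80 at k = 1, and 0.96 to 0.98 at k = 0.5. The article gives no k, so no single figure can be stated.

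**The case against.** The strongest reply is that the outcome list is the formal definition, gives a unit, and agrees with the section on calculated variables. Change appears only in an objective and as a data-collection label. That stands, and it is the reason to settle on residual volume. The mismatch still needs correcting.

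The size of the gain is also uncertain. No r is given. Control patients have the haematoma evacuated, so r may be low and may differ between arms. That stands too: at r = 0.2 the gain is only about 4%.

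The planned subgroup models do use haematoma size, but they test whether the treatment effect varies with size. They do not put baseline volume into the main comparison.

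A reader might infer more than the article supports:

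- *That the unadjusted analysis is biased.* Under randomisation, 3-month volume without baseline is a valid comparison.
- *That adjusting makes the naming irrelevant.* Change and residual give the same adjusted contrast only in a linear model on the raw scale. The article names a generalized linear model, and with another link or a transformed outcome the endpoint still has to be named.
- *That a change score is noisier whenever r is below 0.5.* That needs equal SDs at both times; in general the condition is r < k/2.
- *That transformation is forbidden.* The article calls it not applicable, and a generalized linear model can handle skew through its distribution and link.
- *That a graded baseline mRS is certainly available.* Excluding patients above mRS 3 needs only a judgement against that cut-off. The article describes graded mRS only at follow-up.

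**Conclusion.** The point holds as a matter of endpoint consistency and precision on one secondary outcome. The article names two variables for it, and its covariate rule would usually leave out baseline volume. In a linear model, always adjusting gives variance 0.96 to 0.64 of that for 3-month volume alone over an assumed r of 0.2 to 0.6, equal to about 4% to 56% more patients. This rests on the assumed r and on linearity, so it need not carry over exactly to another link. The estimate of how much the imbalance rule discards also rests on reading uneven as p < 0.05. Validity, the primary analysis and the sample size are not in question.

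**What to change.** 1. Name one endpoint, 3-month residual volume in mL, in the secondary objectives, the outcome list, the data-collection section and the analysis section.
2. Prespecify baseline volume and centre as covariates in its model, regardless of observed balance.
3. State which scan supplies the baseline volume. The eligibility criteria allow CT or MRI at inclusion, whereas follow-up is by CT. The participant timeline lists a week-1 CT without saying whether it precedes treatment. The covariate must be a pre-treatment volume.
4. Reword the section on calculated variables only if a transformed or calculated outcome is to be used.
5. Include baseline mRS in the ordinal mRS models if the graded value is recorded at inclusion.

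The cost is mainly wording, settled before any comparison by arm is seen. The article plans radiological measurements at inclusion without naming volume. If baseline volume has not been recorded, it has to be read from the inclusion scans. No new patient procedures are needed.
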